## Abstract

**Background:**

Internationally, it has been stressed that advance care planning integrated within kidney services can lead to more patients being involved in decisions for end-of-life care. In Denmark, there is no systematic approach to advance care planning and end-of-life care interventions within kidney services. A shared decision-making intervention for planning end-of-life care may support more effective treatment management between patients with end-stage kidney disease, their relatives and the health professionals. The purpose of this research is to find evidence to design a shared decision-making intervention and test its acceptability to patients with end-stage kidney disease, their relatives, and health professionals in Danish kidney services.

**Methods:**

This research project will be conducted from November 2020 to November 2023 and is structured according to the UK Medical Research Council framework for complex intervention design and evaluation research. The development phase research includes mixed method surveys. First, a systematic literature review synthesising primary empirical evidence of patient-involvement interventions for patients with end-stage kidney disease making end-of-life care decisions will be conducted. Second, interview methods will be carried out with patients with end-stage kidney disease, relatives, and health professionals to identify experiences of involvement in decision-making and decisional needs when planning end-of-life care. Findings will inform the co-design of the shared decision-making intervention using an iterative process with our multiple-stakeholder steering committee. A pilot test across five kidney units assessing if the shared decision-making intervention is acceptable and feasible to patients, relatives, and health professionals providing services to support delivery of care in kidney services.

**Discussion:**

This research will provide evidence informing the content and design of a shared decision-making intervention supporting patient-professional planning of end-of-life care for patients with end-stage kidney disease, and assessing its acceptability and feasibility when integrated within Danish kidney units. This research is the first step to innovating the involvement of patients in end-of-life care planning with kidney professionals.

## Background

The purpose of this research is to outline the research methods we will employ to develop a shared decision-making (SDM) intervention to support patients with end-stage kidney disease (ESKD), relatives, and health professionals (HPs) in planning and deciding about end-of-life care (EoLC) together.

### Integrating EoLC decisions in ESKD: a non-consistent pathway

Core activities of kidney services are to help patients with ESKD preserve residual renal function, initiate kidney replacement therapy when needed, and manage patients’ symptoms. Patients with ESKD may have a high symptom burden, e.g., fatigue, pain, dyspnoea, nausea, decreasing physical function, and restless legs [1]. During progression of their disease, patients make adjustments, or plan changes, to their treatment regardless of whether they are treated with dialysis, conservative kidney management, or a kidney transplant. Kidney care services are central to preparing patients with ESKD for EoLC, and palliative care options, as their health continues to deteriorate. Relatives are often involved in planning care with patients as they fit treatments into their lives; in some cases, patients can lose cognitive function and become unable to make decisions meaning relatives make decisions on their behalf [2, 3]. Patients and their relatives may find these decisions difficult. Being involved in decisions about end-of-life (EoL) options earlier in the illness journey is, on the other hand, associated with an amelioration of worry [4–6].

Internationally, the need for integration of palliative care into nephrology services has been stressed [7–9]. Palliative care aims to enhance patient’s quality of life as they transition from treatment of kidney disease to living well at the EoL [10]. Services differ in the way they offer and integrate palliative care options into patient’s kidney disease management, and some patients die with ESKD before having their palliative care needs fulfilled [11]. Models of how to deliver palliative care within ESKD are limited [12, 13]. Advance care planning (ACP) interventions integrated within kidney services can lead to more patients being involved in decisions about their desired level of treatment, and to an appropriate use of palliative care services [14]. ACP is defined as a process supporting adults at any age or stage of health in understanding and sharing their personal values, life goals, and preferences regarding future medical care [15]. Its goal is to enable patients to receive medical care consistent with their values and preferences during serious and chronic illness [15]. However, there are barriers to implementing ACP within kidney services including HPs’ attitude to talking about EoL issues and fears about taking hope from patients and their relatives [4].

### Preparing a consistent pathway

In Denmark, there is no systematic approach to ACP and integrating EoLC options within kidney services. A systematic review by Brinkman-Stoppelenburg et al. from 2014 [16] found that ACP had a positive impact on the quality of EoLC within different patient populations and settings. The authors concluded that when trying to meet the patient preferences complex ACP interventions could be more effective than written documents alone [16]. However, they stated that existing research on what outcome ACP generates is diverse [16]. An SDM framework may support more effective ACP about kidney disease management and EoLC options being made between patients with ESKD, their relatives, and the HPs. Shared decision-making has been defined as an interpersonal, interdependent process in which patients, their relatives, and HPs relate to and influence each other as they collaborate in making decisions about a patient’s health [17]. In Denmark, SDM interventions [18–20] are an acceptable framework to support patients making dialysis modality decisions earlier in the kidney disease pathway. These SDM interventions are informed from research exploring patient and professional decision-making, and they identify practices that support or hinder patient’s engagement with decisions [21–24]. Shared decision-making interventions are complex interventions with components supporting HPs skills (e.g., decision coaching training), patient understanding (patient decision aids), and patient-professional communications (e.g., consultation prompts).

The aim of this research is to find evidence informing the content of an SDM intervention and to test the acceptability and feasibility of the intervention to patients with ESKD, their relatives, and the HPs in kidney services.

### Study protocol

#### Overall aim of the research

To develop, and test the acceptability and feasibility of, an SDM intervention to support EoLC planning and decision-making in patients with ESKD, their relatives, and the HPs in kidney services.

#### Primary specific objectives

To identify component parts for inclusion in an SDM intervention supporting EoLC for kidney disease management in Denmark (phase 1), and test its acceptability and feasibility in usual kidney care services (phase 2).

#### Phase 1—research to design the complex intervention

##### Study 1: identifying evidence—literature review

Scoping review of the literature to identify international primary empirical evidence of evaluated patient involvement interventions for patients with ESKD planning and deciding about their EoLC.

##### Study 2: identifying evidence—patients, their relatives, and HPs’ experiences and needs

Semi-structured interview study describing multiple-stakeholder experiences of involvement in decision-making and decisional needs towards EoLC.

##### Study 3: developing the prototype SDM intervention

To iteratively model and develop an SDM intervention using the active elements of the mixed methods investigations from the scoping review and semi-structured interview study, with reference to international guidelines.To develop a prototype of the SDM intervention with input from the steering committee.To refine the SDM intervention according to the findings and research from study 1 and 2 and the input from the discussions with the experts throughout the developing process to be ready to acceptability testing.

#### Phase 2—acceptability testing of the SDM intervention

##### Study 4: acceptability testing

To test the acceptability and feasibility of the SDM intervention in patients with ESKD, their relatives, and the HPs making ACP and EoLC decisions within kidney services.

## Methods/design

### Framework informing the research methods

The research design and methods are informed by the UK Medical Research Council (UKMRC) framework for complex interventions development and evaluation. The framework identifies four phases of research: development, feasibility/piloting, evaluation, and implementation [25, 26]. This research project addresses the first two phases: (1) intervention development research, and (2) intervention feasibility/piloting testing, referred to as acceptability testing an evidence-based intervention for use in kidney services. As an application to the above-mentioned framework, the Methods of Researching End of Life Care (MORECare) statement, focusing on EoLC will be used supplementary [8]. This statement is providing 36 best practice solutions for researchers evaluating interventions in EoLC. To assure steady contemplation on implementation of the SDM intervention into kidney services, the phases three and four will be continuously considered throughout the two research phases addressed in this project, as outlined in the MORECare statement [8].

### Framework informing the SDM intervention

The Making Informed Decisions, Individually and Together (MIND-IT) framework by Bekker 2015 [27, 28] provides a representation of the components needed to support different people involved in making healthcare decisions. The International Patient Decision Aid Standards (IPDAS) collaboration checklist [29], the Ottawa Decision Support Framework (ODSF) [30, 31], and the inter-professional shared decision-making model (IP-SDM Model) framework [32, 33] provide the frameworks to carry out this research to identify the constituents of this intervention, and plan for its use and evaluation in practice.

### Steering committee oversight

To get a broad support from relevant stakeholders, an integral part of developing a complex intervention is to create a steering committee [34]. In this research, the purpose of the steering committee is to provide oversight of the research processes and outcomes, to provide rigor and relevance of our outputs to the delivery and experience of kidney care. The steering committee includes the PhD supervisory team, consultants, and nurses from participating nephrology units as well as patients and their relatives with experience of ESKD and EoLC decision-making. Steering committee participants will be recruited through the participating nephrology units by the lead staff, the primary investigator, or the co-investigators. The steering committee will be active in helping include study participants and will be invited to participate in two workshops where the research data will be presented and the steering committee will work on developing a prototype of the SDM intervention.

### Patient and public involvement (PPI) in the research process

Our research team includes a person with ESKD and a relative of a patient with ESKD. Their role is to provide a critical appraisal of the research process from two different perspectives, independent of participants in the research studies. We plan for our PPI members continuously to be involved in the research process and its dissemination through participation as co-authors in publications, in steering committee attendances, as commentators on research materials, and in dissemination activities.

### Settings

The phases 1 and 2 research will be conducted at the Department of Renal Medicine, Aarhus University Hospital (AUH) including satellite units in Randers and Horsens, as well as Herlev and Gentofte Hospitals. From these settings, patients with ESKD, their relatives, and HPs will be involved.

### Recruitment

Patients with ESKD on haemodialysis, peritoneal dialysis, or on conservative kidney management and relatives of patients with ESKD will be considered for participation. Eligible patients will be identified using a clinical provider-initiated indicator, the surprise question (SQ): “would you be surprised if this patient died in the next 12 months?” [35]. The HPs may answer the question on a 5-point Likert scale (“definitely not surprised”, “not surprised”, “neutral”, “surprised” or “very surprised”) [36]. Patients who are cognitively unable to participate will be excluded from the research. Participants will be recruited through the departments and satellite units mentioned above, via relevant staff of the participating nephrology units. A clinical staff member, who knows the patients well, will be asked to approach the patients in person and inform them about the project. If a patient is interested in participating, the primary investigator will contact them and provide them the opportunity to ask any questions they may have related to the research. The lead staff of the participating nephrology units together with the primary investigator and the co-investigators will recruit HPs. Patients, relatives, and HPs will be recruited in the same way for studies in both phases of the research. All participants will be asked to complete written consent prior to enrolment into the research.

### Ethics and dissemination

This project will be conducted in agreement with the ethical principles for medical research involving human subjects [37], and involves informed consent for study participation [38]. We will obtain written consent from patients, relatives, and HPs before we conduct interview studies. No adverse events have been reported from SDM intervention studies [39]. Once we have obtained the planned research data, we will obtain approval from the Danish Data Protection Agency for data management [40]. To support integration of EoLC plans into usual care, dissemination and knowledge transfer will be conducted via peer-reviewed publications, through seminars and conferences, via informed decision-making to patients and their relatives, and by decision coaching training for staff.

### Timeline

The research project will be conducted over a period of three years from November 2020 to November 2023. Month 0–23 will focus on phase 1; month 23–36 will concentrate on Phase 2. From month 12, we will start recruiting patients for the semi-structured interviews and from month 23, patients will be recruited for answering the questionnaires.

#### Phase 1—research to design the complex intervention

In phase 1, the evidence and theoretical frameworks to structure the SDM intervention will be identified though survey designs using literature review and interview methods. This phase will address the service needs and practices for patients with ESKD, their relatives, and the HPs towards making EoLC decisions.

##### Study 2: identifying evidence—patients, their relatives, and HPs’ experiences and needs

Individual semi-structured interviews with patients with ESKD, relatives, and HPs in kidney services, will investigate experiences of involvement in the decision-making process, decisional needs, concerns, and values of the participants in relation to planning EoLC when the patients’ health may deteriorate. Sample size of about 12 participants from each stakeholder group, will be recruited using the process described above. The design of the interview guides is based on the interview methods by Kvale and Brinkmann [48] and explore the skills, experiences, reasoning, and motivations of each stakeholder represented within the MIND-IT framework with the Patient Experience of Shared Decision-Making (SHARED) tool [49] will form part of the interview guide. Data from the interviews will be analyzed using a thematic content analysis described by Malterud’s systematic text condensation [50]. This strategy of systematic text condensation to synthesize findings by Malterud is a strategy for qualitative analysis structured upon Amedeo Giorgi’s psychological phenomenological analysis also used towards decision-making [51]. Data will be coded and analyzed in accordance with the four stages of systematic text condensation using the software program NVivo [52]. The evidence gathered from the interview data will be used to inform the design and development of the SDM intervention.

#### Phase 2—acceptability testing of the SDM intervention

In phase 2, the acceptability and feasibility of the SDM intervention will be assessed with patients having ESKD making EoLC decisions, their relatives, and HPs providing the delivery of care in kidney services.

##### Study 4: acceptability testing

A pragmatic, pilot, randomized controlled, non-blinded multicenter superiority trial with two parallel groups will test the acceptability and feasibility of the intervention on patients, relatives, and HPs. The primary endpoint will be decrease in palliative care needs 3 months after receiving the intervention. Secondary endpoints are patient and relative experiences of SDM and HPs conduction of SDM post-intervention. Randomization will be performed as block randomization with 1:1 allocation.

Inclusion criteria will be patients having ESKD who are at a stage in their disease where EoLC has to be considered; age ≥ 18 years old; and alert and oriented. Patients and relatives will be recruited from November 1, 2022 until February 1, 2023. The contact HPs of the eligible patients will be recruiting them and will be allocated to the group where the patients and relatives are allocated. Sample size is dependent on how many patients we are able to recruit to the study by using a clinical indicator and the number of patients willing to participate at the different hospital sites. We hope to recruit around 10 patients for each group.

Bekker’s MIND-IT framework [27, 28] represents the roles of all stakeholders involved in making health decisions and was used to guide the choice of evaluation tools to assess the SDM intervention on patients, relatives, and HPs decision processes and outcomes.

The Integrated Palliative Outcome Score (IPOS)-Renal questionnaire, patient version [53], will be used to measure the primary outcome ‘change in the patient’s palliative care needs. IPOS-Renal is a short measure (11 questions), combining the most common symptoms renal patients experience and additional items from IPOS on concerns beyond symptoms, such as information needs, practical issues, and family anxiety.

The 10-item Patient Experience of Shared Decision-Making (SHARED) tool [49] will measure the degree of which the patients and relatives feel that they have shared in decision-making about their EoLC. Items are rated in a 5-point Likert scale ranging from ‘disagree strongly’ to ‘agree strongly’. Scores are out of 10, with one point for ‘agree’ or ‘agree strongly’, and no points for ‘not sure’, ‘disagree’ or ‘disagree strongly’. Higher scores indicate a more shared decision-making experience.

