### Intervention development and acceptability testing processes

The intervention development phase will consist of three studies using different methods and the acceptability phase of one study using different methods as outlined in Table 1.

**Table 1 Tab1:** SDM development and acceptability testing process

Phase/study	Objective	Framework	Method
**1/1**	To synthesise empirical evidence of patient involvement interventions for patients with ESKD making EoLC decisions in Denmark and internationally	UKMRC MORECare JBI PRISMA-ScR	Literature search through the databases; PubMed, Embase, CINAHL, and Scopus and a Grey literature search. Inclusion/exclusion of literature using Covidence. Scoping review of included literature. Synthesising evidence.
**1/2**	To explore experiences and needs for involvement in EoLC for patients with ESKD, their relatives, and HPs	UKMRC MORECare MIND-IT	Present and carry out semi-structured interviews with patients having ESKD, relatives, and HPs. Around 12 patients, 12 relatives, and 12 HPs will be interviewed.
**1/3**	Synthesising the primary and secondary findings from the research and structure a prototype of the SDM intervention	UKMRC MORECare MIND-IT IPDAS ODSF IP-SDM Model	Based on the synthesised evidence through phase 1, study 1 and 2, and supported by methods for developing SDM interventions and relevant theory, a prototype of the SDM intervention will be developed and evaluated during workshops involving expert consensus from the steering committee.
**2/4**	To test if the SDM intervention for planning EoLC is acceptable to patients with ESKD, their relatives and the HPs	UKMRC MORECare MIND-IT IPDAS	A pragmatic, pilot, randomized controlled, non-blinded multicenter superiority trial design will be used to test the SDM intervention in the participating nephrology units. Different questionnaires will be introduced and carried out to evaluate the patient reported outcomes on the SDM intervention, to evaluate the decision support provided by the HPs, and to evaluate if the intervention leads to better healthcare.

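### Study 4 is an acceptability and feasibility pilot, but its superiority label, efficacy primary endpoint and Table 1 purpose imply an effectiveness conclusion that about 10 patients per group cannot support

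*Protocol article*

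**What the plan says.** In the protocol article, the section on Study 4 (acceptability testing) gives the design as "A pragmatic, pilot, randomized controlled, non-blinded multicenter superiority trial with two parallel groups". The same sentence continues that it "will test the acceptability and feasibility of the intervention on patients, relatives, and HPs". The next sentence sets a directional efficacy endpoint: "The primary endpoint will be decrease in palliative care needs 3 months after receiving the intervention". The instrument is the patient version of IPOS-Renal; experience and conduct of shared decision-making (SHARED, DSAT-10) are secondary.

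On size, the section states that "Sample size is dependent on how many patients we are able to recruit to the study", and then: "We hope to recruit around 10 patients for each group". Allocation is 1:1 in blocks.

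Table 1, in the row for phase 2, study 4, repeats the label ("A pragmatic, pilot, randomized controlled, non-blinded multicenter superiority trial design will be used to test the SDM intervention") and ends its Method cell by saying that the questionnaires serve, among other things, "to evaluate if the intervention leads to better healthcare". The Objective cell of that row mentions acceptability only.

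The rest of the article sets a narrower scope. The overall aim, the objectives and the opening of Phase 2 all speak of acceptability and feasibility. The section on the framework informing the research methods says the project covers the first two of four phases, with evaluation and implementation coming after. The Discussion lists that restriction as a limitation.

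**The concern.** Two descriptions of the same study stand side by side. In one, Study 4 is a pilot that asks whether the intervention is acceptable and workable. In the other, it is a superiority comparison whose only primary endpoint is a clinical benefit and whose questionnaires are meant to show whether care improves. Nothing in the article calls the between-group comparison exploratory, so a reader cannot tell which description governs the conclusions.

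If the second description governs, two errors become likely. A non-significant IPOS-Renal difference may be read as absence of benefit when the trial could hardly have shown one. A significant difference would overstate the effect unless the true effect is very large, because an unadjusted two-sided test at this size is significant only when the observed difference exceeds about 0.94 sample SD. Meanwhile the questions the pilot was set up to answer have no primary outcome of their own.

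**Working it through.** **No figure to reproduce.** The article states no power calculation. The check asks what a superiority comparison of the stated size could show.

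**Inputs from the article:** about 10 patients per group, 1:1 allocation, and a change in IPOS-Renal as primary outcome (section on Study 4).

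**Assumptions, not in the article:** two-sided alpha 0.05; unadjusted two-sample t test; no attrition; true standardized difference d of 0.3 to 0.8, in units of the SD of the analysed outcome. Variations follow below.

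**Formulas.** With n per group, the degrees of freedom are 2n − 2 and the noncentrality is d × √(n/2). For n = 10 these are 18 and 2.236 × d. Power is the probability that the noncentral t statistic lies beyond ± t(0.975, 18) = ± 2.101. The 95% CI half-width in SD units is t(0.975, 18) × √(2/n) = 2.101 × √0.2 = 0.94.

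**Power at 10 per group, and under other assumptions:**

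| Assumptions | d = 0.3 | d = 0.5 | d = 0.8 | d for 80% power |
|---|---|---|---|---|
| Two-sided 5%, unadjusted, 10 per group | 10% | 19% | 40% | 1.33 |
| One-sided 5%, unadjusted, 10 per group | 16% | 29% | 53% | 1.16 |
| Two-sided 5%, baseline-adjusted, correlation 0.7, 10 per group | 14% | 32% | 66% | 0.95 |
| Two-sided 5%, unadjusted, 8 evaluable per group | 9% | 15% | 32% | 1.51 |

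For the baseline-adjusted row, d is in units of the SD of the follow-up score, and adjustment multiplies the residual SD by √(1 − 0.7²) = √0.51 = 0.714. The detectable difference is therefore 1.325 × 0.714 = 0.95 SD, and the CI half-width is 0.94 × 0.714 = 0.67 SD. With 8 evaluable per group the unadjusted half-width is 1.07 SD.

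**How favourable must the assumptions be?** For a two-sided test to reach 80% power at 0.8 SD, 1.325 × √(1 − ρ²) must fall to 0.8. That gives ρ = √(1 − (0.8/1.325)²) = 0.80. The article offers no support for so high a correlation between baseline and follow-up.

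**What a powered comparison would need:** for 80% power with the two-sided unadjusted t test, 176, 64 and 26 per group at d = 0.3, 0.5 and 0.8. These figures show the distance between the framing and the size; they are not a recommendation.

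**The case against.** The strongest reply is that superiority names a type of comparison, as opposed to non-inferiority or equivalence, and says nothing about power. An underpowered superiority trial is still a superiority trial. The article claims no power and promises no proof of benefit. The design sentence itself contains the word pilot and goes on to acceptability and feasibility, and the Discussion limits the work to development and pilot testing. The Table 1 clause is the last part of a Method cell whose Objective cell is confined to acceptability.

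Much of this stands. The label alone would be a small matter, and the article does not claim a power that it lacks. The reply does not cover the combination: the label appears twice, the sole primary endpoint is directional efficacy, and a stated use of the data is to judge whether care improves. Nothing marks that comparison as exploratory.

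Three stronger readings are tempting and should be resisted:

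- **That the trial is too small.** Sizing a pilot by recruitment is ordinary, and the article is open about doing so.
- **That an IPOS-Renal result could wrongly decide whether the next framework phase goes ahead.** The article ties progression to no outcome.
- **That the 1.3 SD threshold is a property of the design.** It depends on alpha, sidedness, adjustment and attrition, none of which the article states.

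Nor can the point be put down to detail left to a full protocol or analysis plan. It rests on statements in the article that pull in different directions.

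**Conclusion.** The point holds as a mismatch between aim and framing. A study whose stated purpose is acceptability and feasibility, and which defers evaluation, is presented with a superiority label, an efficacy-only primary endpoint and an effectiveness purpose, on about 20 patients in total. At that size a between-group difference is estimated to within about ± 0.94 SD (± 0.67 SD with baseline adjustment at correlation 0.7). Power stays at or below 66% for effects up to 0.8 SD in every row of the table. The sizes rest on assumed alpha, test, correlation and attrition. The conclusion would change only if the true effect were near or above 1 SD, or if the correlation between baseline and follow-up were about 0.8 or more with an effect of 0.8 SD. The article argues for neither. The correction is worth making because it changes what the trial may conclude, even though conduct and sample stay as they are.

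**What to change.** 1. Delete the word superiority from the design sentence in the section on Study 4 and from the study 4 row of Table 1. Delete the closing purpose in that row about better care.
2. Make acceptability and feasibility measures the primary outcomes, so that they match the stated aim.
3. Label the IPOS-Renal, SHARED and DSAT-10 comparisons exploratory. Report them as between-group differences with 95% confidence intervals, baseline-adjusted for IPOS-Renal, and state that no efficacy conclusion will be drawn from statistical significance.
4. Report the SD, the correlation between T1 and T3, and attrition, so that the later evaluation can be sized. The article sets T3 at 8 weeks but the primary endpoint at 3 months. That is a separate discrepancy, and it must be reconciled for the correlation to refer to the intended time point.

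The trial should not be enlarged. No patient need be added, and the three questionnaires stay. Measures of acceptability and feasibility must be named as primary, and the stated ambition becomes more modest.
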